**Planned duration of clinical trial:**

Date of approval - December 31, 2023

**Notice**

This document is NOT formal protocol but is the English translation version of the original protocol written in Japanese.

## Revision History

| Edition No. | Effective date    | Author   | Remarks                                                                                                                                                                                                                                                                                                                                                                                                              |
|-------------|-------------------|----------|----------------------------------------------------------------------------------------------------------------------------------------------------------------------------------------------------------------------------------------------------------------------------------------------------------------------------------------------------------------------------------------------------------------------|
| ver 1.0     | December 10, 2018 | [name] | Protocol approved by the St. Marianna University School of Medicine Institutional Ethical Committee (No. 4129).                                                                                                                                                                                                                                                                                                      |
| ver 1.1     | May 13, 2019      | [name] | First revision approved.
-Clarification of wording in protocol and addition/removal of research team members.                                                                                                                                                                                                                                                                                                     |
| ver 1.2     | October 9, 2019   | [name] | Second revision approved.
-It was found that preparing a nursing summary at discharge with detailed deprescribing information was difficult due to time constraints. Since the intervention team already prepared a drug information report as part of the planned intervention, it was deemed unnecessary to prepare a nursing summary for all participants unless required as a part of the usual care process. |
| ver 1.3     | September 8, 2020 | [name] | Third revision approved.
-CTCAE version update
- Change in research team member's affiliation                                                                                                                                                                                                                                                                                                                  |
| ver 1.4     | January 12, 2021  | [name] | Fourth revision approved.
-Extension of the study period due to the delay in study enrollment, partly because of the COVID-19 pandemic.                                                                                                                                                                                                                                                                           |
| ver 1.5     | June 22, 2021     | [name] | Fifth revision approved.
-Extension of the study period due to the delay in study enrollment, partly because of the COVID-19 pandemic.
-Change in research team member's job title                                                                                                                                                                                                                             |
| ver 1.6     | December 2, 2021  | [name] | Sixth revision approved.
-Extension of the study period due to the delay in study enrollment, partly because of the COVID-19 pandemic.                                                                                                                                                                                                                                                                            |
| ver 1.7     | June 21,2023      | [name] | Seventh revision approved.
-Extension of the study period due to delays in data entry.
-Change in research team members' job title and affiliation.                                                                                                                                                                                                                                                            |

|                                                                                          |           |
|------------------------------------------------------------------------------------------|-----------|

## 1. Background

Polypharmacy is a growing social problem that increases hospitalizations and deaths among the elderly, and also leads to higher healthcare costs. As a countermeasure, a list of potentially inappropriate medications that may lead to adverse drug events has been widely used. One list that has been particularly widely disseminated is the Screening Tool of Older Persons' Prescriptions (STOPP). One feature of this list is that it can be used in conjunction with the Screening Tool to Alert to Right Treatment (START) criteria, which summarize recommended treatments that are beneficial to the elderly, along with the STOPP criteria, which summarize potentially inappropriate prescribing in the elderly. The STOPP/START list has been widely used in the United States and Europe. A recent systematic review of randomized controlled trials of deprescribing interventions using STOPP/START showed that STOPP/START interventions were associated with fewer falls, shorter hospital stays, fewer emergency room visits, and lower healthcare costs. However, to date, no improvements in more important outcomes, such as death or rehospitalization, have been demonstrated with the intervention. Limitations of the list of potentially inappropriate medications include the large number of adverse events caused by drugs not included on the list, as well as the possibility that there is both "appropriate polypharmacy" and "inappropriate polypharmacy".

In response to these limitations, "deprescribing protocol", in which the appropriateness of individual prescription medications for each patient is reviewed based on certain criteria, have gained attention. Although protocol-based interventions have been shown to reduce the number of prescribed medications, it has yet to be proven whether these interventions improve important clinical outcomes such as death, hospitalization, and falls. However, it has been suggested that most recent studies have had short follow-up periods of less than one year and may not have detected a true effect. Thus, while polypharmacy intervention is recognized as an important topic worldwide, methodological problems with existing studies have also been highlighted.

## 2. Necessity and objective of the study

In Japan, healthcare policy toward deprescribing through the Comprehensive Drug Evaluation and Adjustment Program started in 2016, and there is a social need to verify whether deprescribing is effective and worth the effort and cost. Furthermore, as mentioned above, if the true efficacy of polypharmacy intervention can be proven in clinical trials addressing methodological limitations of existing research, it is expected to be a globally valuable evidence that will promote the implementation of deprescribing interventions.

This study will examine the effect of multidisciplinary team-based medication optimization on survival, unscheduled hospital visits, and rehospitalization in elderly inpatients with polypharmacy in a single-center, parallel-group comparative trial.

### **3. Overview of the intervention**

A prescription optimization support team consisting of physicians, pharmacists, and nurses reviews the prescriptions of internal medicine inpatients in the intervention group based on STOPP/START and the prescription optimization protocol specifically designed for this study, and makes prescription adjustment proposals after discussion within the team. The name of the drug suggested to be added, reduced, or discontinued, the reason for the change, and the precautions to be taken after the prescription change are generated by the clinical decision support system and provided to the attending physician of the participant. The implementation of prescription changes is left to the discretion of the attending physician as part of usual care.

### **4. Participants**

#### **(1) Inclusion Criteria:**

Patients who meet all of the following criteria will be considered eligible.

1. Medical inpatients admitted to the internal medicine departments of Kawasaki Municipal Tama Hospital (general internal medicine, gastroenterology&hepatology, cardiology, pulmonology, endocrinology, nephrology, and neurology) at Kawasaki Municipal Tama Hospital;
2. Aged 65 years or older;
3. Taking five or more regularly prescribed medications;
4. Predicted length of hospital stay after admission: 1 week or longer;
5. Patients who are deemed eligible to take the drug orally by their attending physician;
6. Patients who have been fully informed of the study and who have given their or their surrogate's free and voluntary written consent based on a thorough understanding of the study.

#### **(2) Exclusion Criteria:**

Patients will not be included in the study if the following apply.

1. Attending physicians disagreeing to study participation;
2. Life expectancy of less than 1 month based on their attending physician's clinical judgement.

### **5. Informed consent**

Prior to participation in this study, all participants will be informed orally and written consent will be obtained. However, if the investigator determines that the participant himself/herself is incapable of making a decision, consent will be obtained from a participant's next of kin (NoK). In this study, a NoK is defined as a person who is justified in giving consent on behalf of the participant based on the relationship and psychological

connection with the participant. In this case, if the NoK is unable to come to the hospital on the same day, he/she will participate in the study with verbal consent by telephone and obtain written consent at a later date. When there is a change in the research protocol that may affect the participant's consent, their intention to participate in the study should be promptly confirmed, and the consent document, should be revised with the prior approval of the President to obtain the participant's consent again.

## 6. Study methods

### ( 1 ) Design

Single-center open-label prospective randomized controlled trial

### ( 2 ) Trial outline (Figure 1)

[figure not shown]

### ( 3 ) Expected duration of participant's enrollment in the study

Participant will enroll in the study from the time of allocation until the completion of 12-month follow-up. During this time, participants will be followed up by periodic telephone interviews.

### ( 4 ) Intervention

The prescription optimization scheme for the intervention group is shown in Figure 2. For subjects assigned to the intervention group after consent is obtained, the prescription optimization support team collects and reviews information and proposes a prescription adjustment plan to the team in charge within 2 days of assignment. Specifically, drug names, blood test data, disease names, etc. are entered into the computerized prescription optimization support system, and the system automatically creates a prescription optimization draft based on STOPP/START. The Prescribing Optimization Support Team, consisting of a physician, pharmacist, and nurse, then conducts a drug review of the subject based on the Prescribing Optimization Protocol (Figure 3) and develops a Prescribing Adjustment Plan. Prescription suggestions (addition, reduction,

discontinuation, etc.), their rationale, and precautions after prescription changes are documented and provided in writing to the physician in charge, leaving the final prescription details to the judgment of the physician in charge. After a change in prescription, if the ward nurse, pharmacist, or physician in charge provides information on any changes that may be related to the prescription, the Prescribing Optimization Support Team will respond as appropriate. At the time of discharge, the Prescription Optimization Support Team will prepare a drug information report after confirming the participant's condition, and provide it to the primary care physician.

Figure 2.

[figure not shown]

Figure 3.

[figure not shown]

## (5) Case registration and allocation methods

### 【Allocation methods】

Patients will be assigned to the deprescribing intervention group and usual care group in a 1:1 ratio by a stratified block randomization method. The allocation factors will be age groups (65-74 years, 75-84 years, and 85 years and older).

### 【Case registration procedure】

The following procedure will be used to enroll cases by the person in charge of the research or a research collaborator.

- (1) Obtain written consent.
- (2) Enter the date consent was obtained and the necessary information to correspond the subject and subject identification code on the subject identification code list kept by the principal investigator.
- (3) Register the case registration form with the subject identification code in eACReSS.
- (4) Receive confirmation of eligibility and a registration confirmation form with the subject registration number and the group to which the subject has been allocated.
- (5) Promptly report to the principal investigator any withdrawal, discontinuation, or dropout.

## **7. Endpoints**

### **( 1 ) Primary endpoint**

- Time to rehospitalization, unscheduled visit, or all-cause death

### **( 2 ) Secondary endpoints**

- All-cause death
- Unscheduled hospital visit
- Rehospitalization
- All-cause deaths during initial hospitalization
- Fall
- Health-related quality of life score (EQ-5D Japanese version)
- Level of long-term care required
- Number of regularly prescribed medications
- Number of potentially inappropriate medications listed in the STOPP criteria version 2.
- Human and time costs of interventions

### **( 3 ) Safety endpoints**

- Adverse events associated with the intervention will be recorded according to CTCAE version 5.0.

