### **<Secondary endpoints>**

After 6 months and 12 months of enrollment, the researcher or research collaborator will contact the participant via telephone and interview about the following information. If it is deemed difficult to interview the participants themselves, a NoK will be asked the same information. Information on medications will be recorded at the time of enrollment and hospital discharge, and inquiries will be made by telephone or fax to the community pharmacy at 6 months and 12 months.

1. Symptoms: To be confirmed by interview.
2. Adverse events: Detailed of events, date of onset/disappearance, degree, treatment required, outcome, severity assessment, and relevance to the intervention will be reported using case report form according to CTCAE version 5.0.
3. Number of medications: Descriptive statistics of the number of medications taken at admission, discharge, and 6 and 12 months after study enrollment and the proportion of drug names.
4. Number of potentially inappropriate prescriptions: Descriptive statistics of the number of potentially inappropriate prescriptions and the proportion of potentially inappropriate drug names. Potentially inappropriate prescriptions are defined as medications that meet STOPP criteria version 2.
5. Health-related quality of life: Measured at baseline, 6 months, and 12 months using the EQ-5D Japanese version. At baseline, a face-to-face survey will be conducted by the researcher, and thereafter, interviews will be conducted via telephone.
6. Level of long-term care required: To be ascertained by interviewing the patient or NoK.
7. Falls and injuries due to falls

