#### **(1) Analysis set**

The analysis of the primary and secondary endpoints will include all study participants enrolled in the study. If it is found that the eligibility criteria are not met after the start of the study, they will be excluded from the analysis. The analysis of the safety endpoints will be performed on all participants enrolled in the study.

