|-----------------------------|---------------------------------------------------------------------------------------------------------------------------------------------------------------------------------------------------------------------------------------------------------------------------------------------------------------------------------------------------------------------------------------------------------------------------------------------------------------------------------------------------------------------------------------------------------------------------------------------------------------------------------------------------------------------------------------------|
| Endpoints                   | 
【Primary endpoint】
 
Time to rehospitalization, unscheduled visit, or all-cause death
 
【Secondary endpoints】
 
 
• Deaths during initial hospitalization
 
• Fall
 
• Unscheduled hospital visit
 
• Health-related quality of life score (EQ-5D Japanese version)
 
• Level of long-term care required
 
• Number of regularly prescribed medications
 
• Number of potentially inappropriate medications listed in the STOPP criteria version
 
• Human and time costs of interventions
 
 
【Safety endpoints】
 
Adverse events associated with the intervention
 |
| Required number of subjects | 500                                                                                                                                                                                                                                                                                                                                                                                                                                                                                                                                                                                                                                                                                         |

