### 10. Safety

#### 10.1 Adverse events

The number of participants in each group who experienced adverse events other than those associated with the primary endpoint and the proportion of such events will be calculated.

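### The stated safety endpoint counts only adverse events attributed to the intervention, no SAP table analyses it, and it conflicts with passages implying that all events are recorded in both groups

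*Combined protocol and SAP*

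**What the plan says.** Protocol section 7(3) has one safety endpoint: "Adverse events associated with the intervention will be recorded according to CTCAE version 5.0". The endpoint list in SAP section 2.1 shortens this to "Adverse events associated with the intervention". Both restrict the endpoint by cause, and the protocol sentence is also phrased as a rule about what is recorded.

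Other parts of the plan are broader. Protocol section 8(3), secondary endpoints item 2, lists the details to be collected for adverse events and ends: "severity assessment, and relevance to the intervention will be reported using case report form according to CTCAE version 5.0". The timetable in section 8 marks adverse events at all six follow-ups without distinguishing the groups. Section 14(1) states: "The analysis of the safety endpoints will be performed on all participants enrolled in the study". Section 14(2) leaves the safety methods to the SAP.

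SAP section 10 sorts events by their relation to the primary endpoint. Section 10.1 counts "The number of participants in each group who experienced adverse events other than those associated with the primary endpoint"; 10.2 and 10.3 break this down by type and severity, and 10.4 is a listing. Sections 10.5 to 10.8 do the same for events that are associated with the primary endpoint.

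On who receives the intervention, protocol section 6(4) says: "For subjects assigned to the intervention group after consent is obtained, the prescription optimization support team collects and reviews information". Section 6(1) describes the trial as: "Single-center open-label prospective randomized controlled trial".

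**The concern.** An endpoint that requires attribution to the study intervention depends on the group by its definition. The control group has no team review and no proposals, so nothing can be attributed to them. Usual care also involves prescription changes and drug harms, and these would fall outside the endpoint. In the intervention group the count depends on a causal judgement made by people who know the allocation, about prescriptions that the attending physician finally decided.

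Two things are at stake. First, the declared safety endpoint has no analysis, so a reader of the report cannot tell which safety result was the planned one. Second, 7(3) and 8(3) item 2 give staff different instructions on what to record. If 7(3) was followed, the per-group tables in SAP 10.1 to 10.3 and the listing in 10.4 would look like a comparison of all other adverse events but would be filtered by attribution.

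**Working it through.** The plan gives no figure for this endpoint, so there is none to reproduce. The check is mainly a comparison of passages.

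**Step 1: what each part implies.**

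| Question | Protocol 7(3), SAP 2.1 | Protocol 8(3) item 2, timetable, 14(1) | SAP 10.1 to 10.8 |
|---|---|---|---|
| Which events? | Only those attributed to the intervention | Adverse events in general | Adverse events in general, split by relation to the primary endpoint |
| In whom? | In effect, the intervention group only | All enrolled participants | Each group |
| Role of attribution | Condition for being counted | One field on the form | Not used |

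A form field for relevance to the intervention has little purpose if only related events are entered. The second and third columns therefore agree with each other, and the first stands apart.

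**Step 2: is the stated endpoint analysed anywhere?** Sections 10.1 to 10.3 and 10.5 to 10.7 are per-group counts and proportions; 10.4 and 10.8 are listings. None selects or tabulates by relation to the intervention. The answer is no.

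**Step 3: what would be exposed if 7(3) governed recording?** Deaths, rehospitalizations and unscheduled visits are collected in both groups under protocol section 8(3) whatever their cause. Falls are too, and SAP 9.2 reports them by group. SAP 9.3 counts an unscheduled visit whatever its reason, and SAP 10.5 to 10.8 cover the primary-endpoint events. The exposed output is SAP 10.1 to 10.4: chiefly adverse events that led to no death, rehospitalization, unscheduled visit or fall. An event during the index stay that caused neither death nor a fall is an example.

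**Step 4: range of the distortion.** Inputs: n = 250 per group (protocol section 15); r, the true proportion with such an event, assumed equal in both groups; a, the share of intervention-group events that staff attribute to the intervention, unknown between 0 and 1.

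- Recorded in the intervention group = n × r × a
- Recorded in usual care = 0
- True difference = 0

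| Assumed r | a = 0 | a = 1 |
|---|---|---|
| 2% | 0 vs 0 | 250 × 0.02 = 5 vs 0 |
| 10% | 0 vs 0 | 250 × 0.10 = 25 vs 0 |
| 20% | 0 vs 0 | 250 × 0.20 = 50 vs 0 |

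The documents give neither r nor a. The right-hand column is an upper bound, reached only if every event in the intervention group is attributed to the intervention. SAP section 10 plans no test, confidence interval or effect measure for these counts.

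**The case against.** The strongest reply is that the working parts of the plan already provide for recording all events in both groups. The form has an attribution field, the timetable applies to everyone, and protocol section 10(2) requires every serious adverse event to be reported whatever its cause. The safety set is all enrolled participants, and the SAP, which the protocol makes responsible for safety methods, tabulates by group without selecting on attribution. On this view 7(3) is one loosely worded line. Both documents also say that they are translations and not the formal text, so one English phrase should not carry too much weight.

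Much of this stands. It makes recording of all events the likelier intention, and it fixes the direction of the correction. It does not explain why the declared endpoint has no analysis, and it does not remove a recording rule that conflicts with another section.

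A reader might go further and infer that the trial can neither show nor exclude a safety difference. The documents do not support that. Even on the strict reading of 7(3), deaths, rehospitalizations, unscheduled visits and falls are compared without attribution. If 8(3) item 2 was followed, SAP 10.1 to 10.3 also give descriptive per-group data on the remaining events.

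A reader might also take 25 versus 0 as the expected result. It is not: an assessor could judge most background events unrelated, and the count could then be close to zero in both groups.

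**Conclusion.** The safety endpoint is wrong as written and should be corrected. As stated in protocol 7(3) and SAP 2.1 it is not a valid between-group measure, and no part of SAP section 10 analyses it. That usual-care patients cannot have such an event is an inference from who receives the intervention; the documents do not say so themselves.

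The effect on results is conditional. If 8(3) item 2 governed recording, the fault is a mislabelled endpoint and a missing attribution summary. If 7(3) governed it, SAP 10.1 to 10.4 are biased between groups by an amount that the documents do not allow one to calculate. With 250 per group and an assumed 10% true harm in both, the range is 0 versus 0 to 25 versus 0. The primary analysis is unaffected, and because no safety test is planned, no error rate is affected either.

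**What to change.** Reword protocol 7(3) and SAP 2.1 so that the safety endpoint is every adverse event from allocation to 12 months, in both groups, regardless of attribution and graded by CTCAE version 5.0. This agrees with protocol 8(3) item 2 and with the tables in SAP section 10. Add to SAP section 10 a descriptive summary of relevance to the intervention, not presented as a between-group comparison. Check the Japanese text so that the original and the translation agree.

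The SAP history shows that version 1.2 followed an analysis already carried out. If data collection has ended, rewording cannot change what was recorded. The report should then state which recording rule was actually applied in each group, and SAP 10.1 to 10.4 should be read in that light.

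The cost is one sentence in each document and one descriptive summary. No new form field is needed if 8(3) item 2 was followed, and sample size and significance level do not change.
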